#### National Cancer Register

The National Cancer Register, managed by the National Board of Health and Welfare, includes all cancer diagnoses in Sweden. Reporting to the register is mandatory by law, and the register includes data on the tumour diagnosis, morphological diagnosis, tumour extent at time of diagnosis, time and place where it was reported, and personal demographic information such as date of birth and place of residence.^23^ The quality of the register is high, with around 99% of the tumours morphologically verified.^31^ The purpose of the register is to follow cancer outcome trends in the population, between subpopulations, as well as contribute to research.

#### National Cause of Death Register

The National Cause of Death Register, managed by the National Board of Health and Welfare, contains reports of all deaths that have occurred in Sweden of residents and non-residents, as well as deaths of residents abroad, including the date and primary cause of death as well as any underlying causes.^26^ When a death occurs, the medical certificate, which is used to determine the underlying cause of death, is filled out by a physician and encompasses a version of the WHO International Form of Medical Certificate of Cause of Death and must be reported within 3 weeks of the event.^26^ The register uses the WHO International Statistical Classification of Diseases and Related Health Problems codes to classify underlying causes of death.^26^ This register additionally acts to monitor causes of death and trends throughout the Swedish population and between subpopulations, as well as contribute to research.

#### National Prescribed Drug Register

The National Prescribed Drug Register, managed by the National Board of Health and Welfare, includes all prescribed drugs distributed in pharmacies in Sweden.^28^ It contains patient, product, prescription, cost and prescriber information.^28^ It includes information on any prescribed drugs dispensed through a pharmacy or on medical devices/consumables.^28^ Trends in prescribed drugs are monitored, and these can additionally be linked to other registers to monitor outcomes.

#### National Patient Register

The National Patient Register, managed by the National Board of Health and Welfare, provides information relating to diseases and specialist care in Sweden.^27^ It includes information on all inpatient stays, outpatient specialised care, compulsory psychiatric admissions and waiting times in emergency departments in Sweden.^27^ Health trends across the country, quality of care and prevention efforts can be monitored with the register.

#### Longitudinal Integration Database for Health Insurance and Labour Market Studies

The LISA Register, managed by Statistics Sweden, collects data on social and economic information on the adult Swedish population. This includes income, main source of income, occupation, sick days, education level and more. The register was initiated to collect data to investigate and address rising levels of sick leave.^24^ The register has been formally collecting data annually since 2003, with data retrospectively until 1990 added by Statistics Sweden using data from the Swedish Public Employment Service, Education Register and the Swedish Social Insurance Agency.^24^ Reporting of this data to the register is compulsory where available and for the general population includes over 95% completeness in income and education reporting.^24^

#### Total Population Register

The Total Population Register, managed by Statistics Sweden, includes every birth, death, emigration from Sweden, immigration to Sweden, migration within Sweden, marriage and divorce, country of birth, legal sex and citizenship.^25^ The primary purpose of this register is to cover the composition and structure of the Swedish population.^25^

### Study population

The study population will include all resident PWH and PWoH, 18 years or older, born between 1940 and 2008, who resided in Sweden at any time point between 1983 and 2024. The study period will span from 1 January 1983 to 31 December 2024. The inclusion date will be the day the person turns 18, the start date of residency in Sweden, or the study start date, whichever occurs last. Follow-up will continue until emigration, death, end of study time or until 6 months before the first incident of CRC. The outcome of interest is CRC. See figure 1 for an illustration of the inclusion criteria and how inclusion and the follow-up period were defined.

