#### Swedish National HIV Register (InfCareHIV)

The InfCareHIV Register includes data on more than 99% of those diagnosed with HIV in Sweden.^7^ When people are diagnosed or when they immigrate to Sweden with an HIV diagnosis, they are informed that their data will be included in the register but that they may opt-out, and that they may opt-out at any time in the future if they are included. InfCareHIV has collected data from all HIV clinics across Sweden since 2003, and earlier data has been retrospectively added.^7^ The register includes demographic variables, such as legal sex and country of birth, as well as variables relating to HIV acquisition such as date of first positive HIV test and the most likely mode of HIV acquisition. At every follow-up visit, routine measures, such as HIV-RNA levels, CD4(+) T cell counts and current ART, are included in the register.

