#### Data preparation

For this study, we will use complete cases only since missing data are minimal. Variables missing more than 10% of the data will be omitted, and after that, any observations with missing data will be dropped.^32^ For the ML analyses, the data will be split 80% into training and 20% into test sets based on follow-up time. The variables in each set will be further prepared to optimise their analysis. Categorical variables will be transformed using one-hot encoding. Normalisation and standardisation of variables will be applied where necessary.

The participants will be matched 1:10 using the entire HIV-negative population in Sweden that fit the criteria. They will be matched on age, legal sex, region of birth and comorbidities including hypertension, chronic obstructive pulmonary disease, diabetes and previous cancer diagnosis.^33
34^ The standardised mean difference of the cohorts will be compared from before and after matching to confirm consistency. Power was calculated using the full anticipated study population consisting of just over 13 000 PWH matched 1:10 to approximately 130 000 PWoH. Median follow-up time is estimated to be at least 10 years in both groups. The expected incidence rate of CRC used for the calculation was the Swedish age-standardised incidence rate reported by the European Commission (129.1 per 100 000 population).^35^ Based on these assumptions and using a two-sided alpha of 0.05, the study is estimated to have 80% power to detect an HR of approximately 1.20 or greater.

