### Clinical relevance

The CRC risk prediction model for PWH will be developed with the aim of supporting risk-stratified CRC surveillance within routine HIV care. The Swedish national CRC screening programme currently invites the general population aged 60–74 years for biennial faecal testing^51^ and does not account for HIV-specific risk factors. A validated risk prediction model could be integrated into the InfCareHIV decision-support interface used at all Swedish HIV clinics, enabling treating physicians at routine annual follow-up to identify individuals who may benefit from earlier screening initiation, shorter screening intervals or referral for colonoscopy. Before clinical deployment, the model will require external validation in independent cohorts and prospective evaluation of its effect on screening uptake, diagnostic yield and stage at diagnosis.

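### The inclusion date leaves out HIV diagnosis, so for people diagnosed later, years before HIV count as PWH follow-up and HIV status is future information at time zero

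*Protocol article*

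**What the plan says.** Under Study population, the rule covers both groups ("The study population will include all resident PWH and PWoH, 18 years or older, born between 1940 and 2008"). It reads: "The inclusion date will be the day the person turns 18, the start date of residency in Sweden, or the study start date", and the latest of these dates applies. The window is fixed ("The study period will span from 1 January 1983 to 31 December 2024"), and so is the end: "Follow-up will continue until emigration, death, end of study time or until 6 months before the first incident of CRC".

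The section on the Swedish National HIV Register says that the register holds the "date of first positive HIV test". It also says that HIV-RNA, CD4 count and current ART are recorded at follow-up visits, and that some people immigrate with a diagnosis already made.

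Data preparation describes the 1:10 matching: "They will be matched on age, legal sex, region of birth and comorbidities". It names no date at which these are measured and no index date for controls.

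Clinical relevance states the intended use: the model would sit in the decision support of HIV clinics, "enabling treating physicians at routine annual follow-up to identify individuals" who may benefit from different screening.

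**The concern.** Three dates are listed, and taking the latest of them closes the list. Followed as written, the rule starts the clock for many PWH long before they had an HIV diagnosis. Four things follow for anyone diagnosed after inclusion:

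- Time without diagnosed HIV is labelled as PWH time.
- The person must stay alive until diagnosis to receive the label, so that time is immortal with respect to death.
- A CRC before the HIV diagnosis could be counted as a PWH event.
- HIV status, CD4, HIV-RNA and ART are not known at time zero. If they are used as baseline predictors, information from the future enters the model.

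At stake is mainly what the model predicts. Risk counted from age 18 or arrival in Sweden is not risk counted from an HIV-clinic visit. Absolute risks, and measures that depend on them such as the Brier score, would be assessed on the wrong time axis. The PWH-only substudy and the missing-data sensitivity analysis state no other time zero.

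**Working it through.** **1. Reading the rule.** Take a lifelong resident born in 1965 with a first positive test in 2005. The 18th birthday falls in 1983, so inclusion is in 1983. Time labelled PWH before HIV is 2005 − 1983 = 22 years. If this person had a CRC in 2000, follow-up would end six months before it and the event would belong to a PWH. A person who arrives in Sweden with HIV is included at arrival, after diagnosis, and has no such time.

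**2. Is it cured elsewhere?** None of Study population, Data preparation, the modelling sections or the PWH-only substudy starts PWH follow-up at diagnosis, makes HIV status time-varying, sets a prediction landmark or gives controls an index date.

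**3. Size of the dilution of the hazard ratio (HR).** Let w be the share of expected CRC in PWH that falls before diagnosis. If that time carries the background rate,

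observed HR = 1 + (1 − w)(HR − 1).

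The documents do not give w, so it is an assumption, shown over a range.

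*(a) Constant CRC rate*, so that w equals the share f of person-time before HIV:

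| f | true HR 1.20 | true HR 1.50 |
|---|---|---|
| 0.10 | 1 + 0.90 × 0.20 = 1.18 | 1 + 0.90 × 0.50 = 1.45 |
| 0.25 | 1.15 | 1.375 |
| 0.50 | 1.10 | 1.25 |

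*(b) CRC hazard rising with the fifth power of age.* Assumed: age at HIV diagnosis mean 37, SD 11; 30 to 70% resident since birth, the others arriving on average 3 years before diagnosis. With uniform birth years, diagnosis in 1983–2024 and no deaths or emigration, pre-HIV time is 6 to 10.6 years per person and 23 to 34% of person-time. It holds only 4 to 6% of expected CRC, because these are young years.

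- w = 0.04: 1.50 becomes 1 + 0.96 × 0.50 = 1.48, and 1.20 becomes 1.19.
- w = 0.06: 1.50 becomes 1.47, and 1.20 becomes 1.19.

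A second run under similar assumptions put 29 to 42% of person-time before HIV and gave 1.45 to 1.47 and 1.18 to 1.19. The value 1.45 corresponds to w = 0.10.

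*(c) Survival condition.* The formula leaves it out. In the limit where nobody with a CRC before HIV goes on to be labelled PWH, observed HR = (1 − w) × HR. With w = 0.04 to 0.10, 1.50 becomes 1.44 to 1.35, and 1.20 becomes 1.15 to 1.08. This is an extreme, since some people survive CRC.

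**4. The power statement, because moving time zero changes its follow-up.** Inputs from Data preparation: 13,000 PWH, 130,000 controls, 129.1 per 100,000 (read as per year), at least 10 years, two-sided alpha 0.05, HR 1.20, 80% power.

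- Events at 10 years: 0.001291 × 10 × (130,000 + 1.20 × 13,000) = 1,880.
- Events needed (Schoenfeld, PWH share 1/11): (1.96 + 0.84)² / [(1/11)(10/11)(ln 1.20)²], about 2,858.
- Power at 10 years is 62%. The stated 80% needs about 15.2 years, which a median of at least 10 does not exclude. That gap is a separate matter and does not decide this point.

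If the 10 years include pre-HIV time and that time is removed, 7.5 years leave 1,410 events and 5 years leave 940. The HR detectable with 80% power goes from 1.25 (full 10 years) to 1.30 or 1.37.

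**The case against.** The best defence is that part of the definition is out of sight. Study population points to a figure for how inclusion and follow-up were defined, and the variable definitions are in a supplement. Time-updated HIV status is often left to an analysis plan, and it would remove the misclassification. This lowers certainty about what will be done, but it does not clear the text: a figure that added a diagnosis date would contradict the written rule.

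Second, the aim is prediction and variable importance. An HR appears only in the power statement, and the dilution is small when CRC is driven by age. This stands, and it is why the point rests on the prediction target. It is also fair that the rule defines follow-up and not a prediction origin. That risk is predicted from inclusion is an inference, drawn because no other origin is given.

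A reader might infer more than the documents support:

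- *No HIV information exists at baseline.* Too broad: people who immigrate with HIV, or were diagnosed before 18, have it.
- *Matching on comorbidities is nearly empty because it is done at age 18.* No measurement date is given, and entry is not always at 18: someone born in 1940 enters in 1983 at about 43.
- *Mortality in PWH is understated.* Mortality is not a study outcome.
- *The HIV effect is strongly diluted or pushed below the null.* Nothing in the documents shows this. The larger dilutions above need a constant CRC rate or the extreme survival case.

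**Conclusion.** The point holds on the text. The stated time zero omits HIV diagnosis, and for people diagnosed after inclusion it labels pre-HIV years as PWH follow-up and makes HIV status and HIV measurements future information. The harm that does not depend on any assumed figure is the mismatch between the time axis of the model and its use in HIV clinics, with its effect on absolute risk and calibration.

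Attenuation of the HR is probably modest: about 1.45 to 1.48 for a true 1.50, and 1.18 to 1.19 for a true 1.20, if CRC rises steeply with age and pre-HIV time carries the background rate. The survival condition would add to this by an unknown amount. The ages at diagnosis and the residency pattern are assumptions, and the linked registers can replace them.

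**What to change.** For PWH, add the date of first positive HIV test to the dates of which the latest applies. For those arriving with HIV, start of residency then normally stays the latest. Give each matched control the index date of its PWH, and require the control to be alive, resident, CRC-free and HIV-negative on that date. Measure matching factors and baseline predictors at that date, and censor a control at a later positive test. Bring the inclusion figure into line.

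Two alternatives are acceptable: treat HIV status as time-varying, so that pre-HIV time counts as time without HIV, or landmark at HIV-care visits, which is closest to the intended use. Whichever is chosen, state the prediction origin.

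The cost is small before analysis, because the register already holds the date. Under the index-date option, pre-HIV person-time is lost. The follow-up assumption and the power statement in Data preparation must be recomputed on post-diagnosis time, and the detectable HR may rise as shown above.

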**Methods and analysis:**

The study population will include all PWH and PWoH born between 1940 and 2008, aged 18 or older and living in Sweden sometime between 1983 and 2024. The study population will be linked to six nationwide demographic and healthcare registers. Follow-up will continue until the first incident of CRC, emigration or death. The outcome of interest is CRC. PWH will be matched to negative controls 1:10. A Cox regression analysis will be completed first, and the results will be used as a baseline comparison to the ensemble ML results. A range of ML methods will be used to develop the ensemble model using stacking.

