#### Cox PH regression

A Cox PH regression model will be used as a baseline performance comparison for the ML methods. This model will favour the simplest approach, and the use of prior knowledge supported by literature will select the most relevant variables. The model performance will then be considered to develop the model for the prediction of cancer among PWH.

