#### Stacking and dissemination

Stacking, an ensemble learning method, will be used to combine predictions from the previously described ML models.^43^ The base learners will generate out-of-fold risk scores using Time Series Split, which will then serve as inputs to a Cox-PH model as the meta-learner. Finally, the trained base learners and meta-learner will then be used to generate final risk score predictions on the test set.

The performance of the stacked models will be primarily evaluated using balanced accuracy,^44^ and additionally assessed with the concordance index,^45^ Brier score,^46^ time-dependent area under the curve and area under the precision-recall curve (AUPRC), before variable importance is assessed.^13
47
48^ All metrics will be thoroughly considered, but the balanced accuracy of each prediction performance will be weighted most due to its handling of class imbalance, considering both sensitivity and specificity.^44^ AUPRC is preferred over area under the receiver operating curve due to its ability to better handle class imbalance, which will be a factor in this study.^49^

The model reporting will adhere to the TRIPOD+AI statement.^50^ The variable importance results will additionally be considered separately. A summary of the analysis plan is illustrated in figure 2.

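### Follow-up ends six months before CRC for future cases only, which contradicts the abstract and leaves event timing, and possibly predictor timing, dependent on the outcome

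*Protocol article*

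**What the plan says.** Protocol article, Study population: "Follow-up will continue until emigration, death, end of study time or until 6 months before the first incident of CRC". The next sentence names the endpoint: "The outcome of interest is CRC". The calendar limits are fixed there too: "The study period will span from 1 January 1983 to 31 December 2024". Inclusion is the latest of the 18th birthday, the start of Swedish residency and the study start.

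Abstract, Methods and analysis: "Follow-up will continue until the first incident of CRC, emigration or death". It has no offset.

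The end date feeds directly into the analysis. Under Cox PH regression: "A Cox PH regression model will be used as a baseline performance comparison for the ML methods". Under Stacking and dissemination, the base learners produce risk scores "which will then serve as inputs to a Cox-PH model as the meta-learner". Under Data preparation, "the data will be split 80% into training and 20% into test sets based on follow-up time".

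The visible text gives no reason for the six months. It does not say whether the event is moved to the earlier date, what happens to a CRC diagnosed within six months of inclusion, or whether non-cases receive a matching lag. Figure 1, cited for the follow-up definition, and supplemental table 1, cited for the variables, are not available here.

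**The concern.** A survival analysis needs one rule for when observation stops and when the event occurs, and that rule must not use information from after the stopping time. The Methods rule breaks this condition: the cut can be placed only by someone who knows that a diagnosis follows six months later.

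Three things are at stake:

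- **Event date.** The abstract and the Methods lead to different survival times for every case, in the Cox comparator, the base learners and the Cox meta-learner.
- **Risk sets.** Moving the event earlier for cases while leaving all other end dates in place creates impossible follow-up times at the start and event-free time at the end.
- **Predictor windows.** If predictor values run up to the end of follow-up, the last six months are removed for cases and kept for non-cases, including the months before a death. Flexible learners could pick up that difference. At the routine annual visit described under Clinical relevance, nobody knows who is six months from diagnosis, so the same cut could not be made.

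The probable aim, keeping pre-diagnostic work-up out of the predictors, is legitimate. The difficulty is that the offset is attached to follow-up, and to cases alone.

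**Working it through.** **The two rules for a person diagnosed at time t after inclusion**

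| | Abstract | Study population |
|---|---|---|
| CRC | t | t − 0.5 years |
| Death or emigration | at that date | at that date |
| End of study | not mentioned | 31 December 2024 |

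Leaving end of study out of an abstract is ordinary shortening. The change from t to t − 0.5 is a difference of substance.

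**Reading A: follow-up stops at t − 0.5 and the event stays at t.** Since t > t − 0.5 for every t, the diagnosis always lies outside follow-up.

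**Reading B: the event is back-dated to t − 0.5.**

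- If t ≤ 0.5, follow-up is zero or negative. The article gives no handling for this.
- If the last diagnosis captured is on 31 December 2024, the latest possible back-dated event is at the end of June 2024. July to December 2024 then has no events, while people without CRC still count as at risk. That is 0.5 of 42 years, about 1.2% of calendar time.
- Moving every end date back by the same six months would amount to a uniform lag. The fault is that only CRC is moved.

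**Scale.** The article gives no figure for this rule, so the inputs are its planning values from Data preparation: 13,000 PWH, 130,000 PWoH and a CRC rate of 129.1 per 100,000, taken as per person-year. Assumptions are a mean follow-up of 10 years (the article gives this as a lower bound for the median) and no excess risk in PWH.

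- PWH: 13,000 × 10 × 0.001291 = 168 cases
- PWoH: 130,000 × 10 × 0.001291 = 1,678 cases
- Total: 1,846 cases
- Person-time removed: 1,846 × 0.5 = 923 person-years
- Total person-time: 143,000 × 10 = 1,430,000 person-years
- Share removed: 923 / 1,430,000 = about 0.065%
- Cases with t ≤ 0.5 under a constant hazard: 143,000 × 0.5 × 0.001291 = about 92, or 5% of 1,846

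A simulation on the same inputs (143,000 people, constant hazard, 10 years) gave 1,873 cases. None had the diagnosis inside follow-up under Reading A. Under Reading B, 93 had zero or negative follow-up, and no event fell in the last six months, against 88 when events were left at the diagnosis date.

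**Effect on power.** Schoenfeld power is Φ(ln HR × √(D × p(1 − p)) − 1.96), with p = 1/11. At HR 1.20 over 10 years, expected events are 1,678 + 168 × 1.2, about 1,880, and power is 62%. Removing the roughly 94 cases with t ≤ 0.5 (92 plus the HIV excess) leaves about 1,786 events and 60%. The article's 80% needs 2,858 events, or a mean follow-up of about 15 years, which its lower bound on the median does not exclude. That is a separate matter and this point does not depend on it.

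**The case against.** The other side has several fair points.

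- **Zero events.** A reader might infer that the study would analyse no CRC events at all. The documents do not support that: CRC is named as the outcome and Cox models are to be fitted to it, so the authors must intend some event coding. What stands is that the coding is not stated in the visible text. Figure 1 may clarify it, but could not remove the conflict with the abstract or the cases-only wording.
- **Predictor leakage.** A reader might infer that the learners will exploit different predictor windows. That requires predictors measured up to the end of follow-up. The InfCareHIV section says that values are recorded at each visit, and Time Series Split suggests time-indexed data, but nothing visible says which values enter the models. If predictors are fixed at inclusion or at matching, cutting the end of follow-up changes no predictor value. This harm is therefore conditional.
- **Size.** The lost person-time and the change in power are both small. The 5% with zero or negative follow-up is probably high. With births from 1940 and a 1983 start, anyone resident at study start enters at 43 or younger, where CRC is presumably rarer. It could differ if entry is reset at matching or HIV diagnosis, which the article does not state.
- **Precedence.** The Methods section is the fuller text, so the abstract does not govern merely by differing. This stands. The reason to prefer the diagnosis date is that it can be set without knowing the future.

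**Conclusion.** The concern holds in this form. The Methods rule conflicts with the abstract, applies its offset to future cases only, and cannot be implemented without an unstated choice about the event date. Either available reading gives faulty event timing: diagnoses outside follow-up, or impossible follow-up times at the start together with an event-free final half-year. The final half-year conclusion assumes that diagnoses are ascertained only to 31 December 2024. Its effect on the hazard depends on the time scale, which is not given.

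Different predictor windows for cases and non-cases follow only if predictors are updated over time or taken near the end of follow-up. The article is silent on this.

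The size is about 923 of 1.43 million person-years (about 0.065%), on the planning figures with 10 years' mean follow-up. This is not a problem of lost data or lost power, and the figures would not support presenting it as one. It still needs correcting before analysis, because the rule sets the outcome time for every survival model and may also enter the train/test split through follow-up time.

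**What to change.** 1. Use the CRC diagnosis date as both the event date and the end of follow-up for every case. Leave emigration, death and end of study as they are. Word the abstract and the Study population section identically.

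2. If pre-diagnostic work-up is to be kept out of the predictors, apply the six-month gap equally to cases and non-cases, in one of two ways:
   - start the risk period six months after each index or prediction date, so that values recorded at the visit remain usable; or
   - use only predictor values at least six months old, for everyone.

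3. State when predictors are measured relative to the index or prediction date.

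The cost is a wording change and one uniform step in data preparation. Under the delayed start, CRC in the first six months after index is not counted: about 92 of 1,846 cases for a single index date, on the constant-hazard planning figures above. Under the lag, the tool ignores the most recent values, including those recorded at the annual visit where it is meant to be used. For that intended use, the delayed start looks the better fit.

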#### ML ensemble model—supervised ML

Elastic Net regularisation, XGBoost, Random Survival Forests and decision trees will be used to develop the ensemble model for predicting CRC risk. For Elastic Net regularisation, a Cox PH model with an Elastic Net penalty will be used to estimate relative risk and interpret variable importance via the penalised regression coefficients. The resulting model additionally highlights influential predictors by minimising less important coefficients towards zero, indicating lower contribution to predicting the outcome.^40^

Decision trees are tree-based models that split data based on variable thresholds to make predictions. Decision trees suited for survival time-to-event data will be used. This method will estimate the probability of cancer over time. This model may additionally be used to infer how much each variable contributes to reducing dataset impurity at each split,^41^ contributing to our understanding of which variables are most valuable to the outcome prediction. Random Survival Forest models work similarly to decision trees but aggregate results across many trees, providing more robust estimates of variable importance and potentially improved performance for risk prediction. XGBoost uses built-in optimisation techniques to develop high-performing prediction models.^42^ The output of the XGBoost model may additionally be used to assess the predictive value of individual variables.

Out-of-fold predictions from each model will be stored to serve as inputs for the meta-learner. Additionally, SHapley Additive exPlanations (SHAP) values will be computed for each trained base learner to assess variable contributions and enhance model transparency.

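### Death is named only as an end of follow-up and CRC is modelled as a single event, so absolute CRC risks taken as 1 minus survival would be too high, most where mortality is high

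*Protocol article*

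**What the plan says.** All references are to the protocol article.

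- **Follow-up.** Study population: "Follow-up will continue until emigration, death, end of study time or until 6 months before the first incident of CRC". The abstract has "Follow-up will continue until the first incident of CRC, emigration or death". In both places death is an end of follow-up and not an event type. (The six-month difference between the two sentences is not the subject here.)
- **Outcome.** Study population: "The outcome of interest is CRC". No other outcome is named.
- **Models.** Cox PH regression: "A Cox PH regression model will be used as a baseline performance comparison for the ML methods". Supervised ML: "Elastic Net regularisation, XGBoost, Random Survival Forests and decision trees will be used to develop the ensemble model for predicting CRC risk". The elastic net is a penalised Cox model and the trees are survival trees. The objective used for XGBoost is not given. Under Stacking and dissemination, the base learners supply out-of-fold scores, "which will then serve as inputs to a Cox-PH model as the meta-learner".
- **Absolute risk.** Of the survival trees, the supervised ML section says: "This method will estimate the probability of cancer over time".
- **Scoring.** Balanced accuracy is primary. The other metrics are the concordance index, the Brier score, "time-dependent area under the curve and area under the precision-recall curve (AUPRC").

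The article mentions no competing risk, cumulative incidence or model for death, and states no prediction horizon. Dates and causes of death are available from the National Cause of Death Register. The Clinical relevance section foresees use for decisions about individuals' screening.

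**The concern.** Someone who emigrates may still develop CRC unseen. Someone who dies cannot. If both are censored alike, a survival model estimates the CRC risk that would apply if death from other causes did not occur. That is harmless for cause-specific hazard ratios and for ordering people by CRC hazard. It is wrong for a statement such as a 10-year probability of CRC.

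The excess grows with mortality and with the horizon, so no single rescaling removes it. It would be larger in older and sicker people. It would also be larger in PWH if their mortality is higher, as the Introduction reports for non-AIDS cancers. Follow-up can run for up to 42 years (1983 to 2024) and to age 84 (birth year 1940), so long horizons are possible. At stake are calibration and any use of the predicted probability as an individual risk. The Brier score and time-dependent AUC are affected too, because both depend on each person's status at the horizon.

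**Working it through.** **Inputs.** The CRC rate is 129.1 per 100 000 (Data preparation), read as a yearly rate, so h = 0.001291. The death rate m is not in the documents and is assumed at 0.2%, 0.5%, 1%, 2% and 4% per year. Both hazards are held constant. The article gives no absolute-risk figure to reproduce, and its power figure does not depend on this point.

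**Formulas.**

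- Death censored: 1 − S(t) = 1 − exp(−h·t)
- Death competing: CIF(t) = h/(h+m) × [1 − exp(−(h+m)·t)]

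**Worked case, t = 10, m = 0.02.** 1 − exp(−0.01291) = 1.283%. CIF = 0.001291/0.021291 × [1 − exp(−0.21291)] = 0.0606 × 0.1918 = 1.163%. The ratio is 1.10.

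| Assumed deaths per year | 10-year CIF (against 1 − S = 1.283%) | Ratio, 10 y | Ratio, 20 y (1 − S = 2.549%) | Ratio, 30 y (1 − S = 3.799%) |
|---|---|---|---|---|
| 0.2% | 1.270% | 1.01 | 1.02 | 1.03 |
| 0.5% | 1.251% | 1.03 | 1.05 | 1.08 |
| 1% | 1.221% | 1.05 | 1.10 | 1.16 |
| 2% | 1.163% | 1.10 | 1.21 | 1.33 |
| 4% | 1.058% | 1.21 | 1.45 | 1.71 |

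In absolute terms the 10-year excess runs from 0.013 to 0.225 percentage points.

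**Scoring.** Take two groups of equal size with assumed CRC hazards h/2 and 2h, at 10 years. With death censored, the risks p are 0.643% and 2.549%. Let c be the corresponding CIF.

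- Brier score of the 1 − S predictions: mean of p(1−p) against the death-censored target, and mean of c(1−p)² + (1−c)p² against what actually happens.
- AUC: the chance that a case ranks above a non-case, ties counted as one half, using p for the censored target and c for the real one.

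| Assumed mortality (low-, high-CRC group) | c | AUC, death censored | AUC, deaths as non-events | Brier, death censored | Brier, deaths as non-events |
|---|---|---|---|---|---|
| 0.3%, 3% | 0.634%, 2.204% | 0.652 | 0.640 | 0.01562 | 0.01393 |
| 3%, 0.3% | 0.556%, 2.511% | 0.652 | 0.662 | 0.01562 | 0.01501 |

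The AUC is too high in the first row and too low in the second. In the first row, predicting with c instead of p gives a real Brier score of 0.01392 against 0.01393. The target shifts visibly, while the gap between the two sets of predictions is very small.

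**The case against.** The strongest reply is that ending follow-up at death is not in itself an error, since a competing-risk analysis does the same. The article does not say how deaths are coded in a model or a metric, it condenses a longer plan, and it refers to external code. So a reader who infers that death is never modelled goes too far: the claim holds only for this article. What remains is that the article fixes CRC as the only outcome, describes its models for that single event, and promises a probability over time. Followed as written, that gives the overstatement shown.

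Other parts of the reply stand in full:

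- A reader might infer that the Brier score and AUC are biased upward. For the AUC this is not so, since its direction depends on how mortality relates to CRC risk.
- A reader might infer that the Cox-versus-ensemble comparison is distorted. This is not shown. Both sides would handle death alike, and the Brier gap in the worked case is 0.00001.
- Balanced accuracy is primary and the stacked output is a risk score, so the main results lean on ranking, which is less affected. Only the survival trees are explicitly said to yield a probability.
- Larger figures can be produced. At 5% deaths per year the 10-year risk is 1.28% against 1.01%, and the 20-year excess is 58%. But constant mortality at that level means 1 − exp(−0.05 × 20) = 63% dead at 20 years. That is an extreme case and the conclusion does not rest on it.
- The article asks for external validation and prospective evaluation before clinical use.

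**Conclusion.** The point holds for absolute risk, calibration and the target of the horizon-based metrics. Any CRC probability read as 1 minus survival, with deaths censored, is too high, and more so in people with higher mortality. The 10-year overstatement is about 1% to 21% in relative terms. At 20 years it is 2% to 45% and at 30 years 3% to 71%. These sizes rest on constant hazards, on reading 129.1 per 100 000 as an annual rate, and on an assumed mortality of 0.2% to 4% per year. The direction for absolute risk does not depend on the mortality chosen.

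Cause-specific hazard ratios and rankings are not invalidated. The documents support neither a general upward bias in the AUC nor a changed winner between Cox and ensemble. The matter should be settled before analysis, because the intended use is individual risk.

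**What to change.** 1. Declare death a competing event and state the prediction horizon or horizons.
2. Keep the cause-specific Cox, elastic-net and stacked risk scores for ranking. The other base learners, XGBoost included, can still feed the meta-learner as scores.
3. Obtain absolute risk as cumulative incidence, by combining the final CRC Cox model (the baseline model or the meta-learner) with one cause-specific model for death. Where probabilities from the survival forest are used, use its competing-risk version.
4. In the test set, score people who died before the horizon as known non-events in the Brier score, the time-dependent AUC and calibration. Treat only emigration and end of study as censoring.

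**Cost.** Protocol wording, a declared horizon, one model for death, and competing-risk versions of the metrics. Dates of death come from a register already among the data sources, so no new data are needed. The downside is a modest amount of extra analysis work.
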